### Data Collection

A standardized pain diary (Multimedia Appendix 1) will be used for collecting the primary outcome and some of the secondary outcomes, such as medication taken over 24 hours. Specific forms will be used for other secondary outcomes, which are available through REDCap. The data will be stored in a password-protected, secure database via REDCap. The data collected will be deidentified and assigned a study code. The pain management unit will be the custodian of the data stored in the password-protected drive within the local health district computer, with access restricted to the investigators only. The data will be stored for 7 years after the completion of the study. Table 1 summarizes the data collection points.

**Table 1. T1:** Data collection points.

Measure	Frequency	Collection points
Pain diaries	Daily	Baseline, week 1, week 2, week 3, and week 4
Average pain over 24 hours (numerical rating scale)	Weekly	Baseline, week 1, week 2, week 3, and week 4
Medications	Weekly	Baseline, week 1, week 2, week 3, and week 4
Patient-Specific Functional Scale	Fortnightly	Baseline, week 2, and week 4
21-item Depression, Anxiety, and Stress Scale	Fortnightly	Baseline, week 2, and week 4
Pain sites update	1 time	Baseline
Pain duration	1 time	Baseline
Demographics	1 time	Baseline

### Power Calculation

Power was planned for the primary within-subject comparison (paired difference between TENS with self-selected music and TENS), with a 2-sided *α*=.05 and 80% power. In the absence of previous variance data, sensitivity analyses were conducted across standardized paired effect sizes (dz). The required numbers of completed pairs (participants who complete both study periods) are presented in Table 2.

**Table 2. T2:** Sample size calculation.

Effect size (dz)	Completed pairs needed, n	Recruits with 10% dropout, n	Recruits with 20% dropouts, n	Recruits with 30% dropouts, n
0.4	52	57	62	68
0.5	34	37	41	44
0.6	24	26	29	31
0.7	19	21	23	25
0.8	15	17	18	20

As a pilot study (target recruitment N=20), the trial is adequately powered only for larger effects (approximately dz≥0.70). Therefore, the primary purpose of this pilot study is to assess the feasibility, estimate variance, and provide effect size estimates to inform the definitive sample size for the main trial.

All calculations were performed using G*Power version 3.1 (Heinrich Heine University), which is widely used for sample size and power analysis in clinical research.

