Intention-to-treat principles will be followed, analyzing participants according to their randomized sequence regardless of adherence or protocol deviations. Mixed-effects models allow inclusion of all available data, including partial data from participants who drop out after the first period, thereby minimizing bias. Per-protocol analyses will be conducted as sensitivity checks. Missing data will be handled descriptively, with analyses restricted to available cases. No multiple imputation will be attempted due to the small sample size.

As a feasibility study with 20 participants, the trial is powered only to detect large effects (approximately dz≥0.70). The observed variance and effect sizes will be used to refine sample size calculations for the definitive trial.

All analyses will be conducted using Stata and SPSS Statistics (IBM Corp).

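### Table 2 inflates for dropout by multiplying by (1+d) rather than dividing by (1−d), so 14 of 15 recruit numbers are too low; separately, the dz≥0.70 statement for 20 recruits carries no dropout condition

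*Protocol article*

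**What the plan says.** The Power Calculation section of the protocol article states the basis of its figures: "Power was planned for the primary within-subject comparison (paired difference between TENS with self-selected music and TENS", "with a 2-sided *α*=.05 and 80% power". No variance data were available, so "sensitivity analyses were conducted across standardized paired effect sizes (dz" of 0.4 to 0.8. The base quantity is defined explicitly: "The required numbers of completed pairs (participants who complete both study periods) are presented in Table 2". Three further columns follow, headed "Recruits with 10% dropout, n", "Recruits with 20% dropouts, n" and the equivalent for 30%. The inflation formula is not given, and the section attributes all calculations to G*Power.

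Below the table the section concludes: "As a pilot study (target recruitment N=20), the trial is adequately powered only for larger effects (approximately dz≥0.70". Statistical Methods repeats this for 20 participants: "the trial is powered only to detect large effects (approximately dz≥0.70". Neither sentence names a dropout rate.

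**The concern.** A column of recruits at a given dropout should list the number to enrol so that the required completed pairs remain. If a fraction d is lost, that number is n/(1−d). Adding d to n instead falls short, because the loss applies to everyone recruited and not only to the n who are needed. The printed figures look like the second calculation.

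The statement about 20 recruits raises a different question. The row for dz=0.7 requires 19 completed pairs, and its recruit numbers (21, 23 and 25) are all above 20. The reader cannot tell at what dropout the statement is meant to hold.

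At stake are the document's only sample-size figures and the chance that the same inflation rule is used again when the larger trial is sized. Dropout is one of the pilot's primary feasibility outcomes, and it is the input that this step uses.

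**Working it through.** **Inputs** (Power Calculation): two-sided α=0.05; 80% power; paired comparison; dz = 0.4, 0.5, 0.6, 0.7, 0.8; dropout d = 0.10, 0.20, 0.30; 20 recruits.

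**Step 1: the completed-pairs column.** Power of the paired t test with n pairs is P(|T| > t(0.975; n−1)), where T is noncentral t with n−1 degrees of freedom and noncentrality dz·√n. The smallest n with power of at least 80% is 52, 34, 24, 19 and 15, which matches all five rows. One pair fewer gives 79.99%, 79.5%, 78.5%, 79.9% and 79.0%. This column is correct.

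**Step 2: the rule behind the recruit columns.** The table compares n×(1+d) with the printed cells, and then with n/(1−d) rounded up. Entries are for 10/20/30% dropout.

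| dz | n | n×(1+d) | Printed | n/(1−d) | Rounded up | Shortfall |
|---|---|---|---|---|---|---|
| 0.4 | 52 | 57.2/62.4/67.6 | 57/62/68 | 57.78/65.00/74.29 | 58/65/75 | 1/3/7 |
| 0.5 | 34 | 37.4/40.8/44.2 | 37/41/44 | 37.78/42.50/48.57 | 38/43/49 | 1/2/5 |
| 0.6 | 24 | 26.4/28.8/31.2 | 26/29/31 | 26.67/30.00/34.29 | 27/30/35 | 1/1/4 |
| 0.7 | 19 | 20.9/22.8/24.7 | 21/23/25 | 21.11/23.75/27.14 | 22/24/28 | 1/1/3 |
| 0.8 | 15 | 16.5/18.0/19.5 | 17/18/20 | 16.67/18.75/21.43 | 17/19/22 | 0/1/2 |

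n×(1+d), rounded to nearest with halves up, reproduces all 15 printed cells. n/(1−d) rounded up agrees with one (dz 0.8 at 10%). Rounded to nearest, it agrees with two (also dz 0.7 at 10%), so 13 remain too low. Rounding n/(1−d) down does not reproduce the table either: at dz 0.4 and 30% it gives 74, against 68 printed.

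**Step 3: what the printed recruits deliver.** Recruiting n(1+d) leaves n(1+d)(1−d) = n(1−d²) pairs, which is 99%, 96% and 91% of the requirement at 10%, 20% and 30% dropout. For the 30% column, with power at the completed pairs rounded down:

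- dz 0.4: 68 × 0.7 = 47.6 pairs, 52 needed; power at 47 pairs about 77%
- dz 0.5: 44 × 0.7 = 30.8 pairs, 34 needed; power at 30 pairs about 75%
- dz 0.6: 31 × 0.7 = 21.7 pairs, 24 needed; power at 21 pairs about 74%
- dz 0.7: 25 × 0.7 = 17.5 pairs, 19 needed; power at 17 pairs about 77%
- dz 0.8: 20 × 0.7 = 14 pairs, 15 needed; power at 14 pairs about 79%

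**Step 4: what 20 recruits deliver.** This uses the same power formula, solved for dz at 80% power.

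| Dropout | Pairs | Detectable dz | Power at dz=0.70 |
|---|---|---|---|
| 0% | 20 | 0.66 | 84% |
| 10% | 18 | 0.70 | 80% (79.9%) |
| 20% | 16 | 0.75 | 74% |
| 30% | 14 | 0.81 | 68% |

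**The case against.** The strongest reply is that nothing in this pilot is sized from the faulty columns. The Discussion (Anticipated Findings) attributes the small number of participants to limits on resources and time. The primary outcome is feasibility, reported descriptively with confidence intervals, and the pain comparison is exploratory. The article also says plainly that it does not expect to demonstrate an added analgesic benefit at this size. All of that stands and limits the weight of the point.

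The size of the error can also be put more mildly. No cell is off by more than 1 recruit at 10% dropout or by more than 3 at 20%. Only five cells are off by more than 2, and the shortfall of 7 occurs in one cell far from N=20. This is correct, but it does not make the columns right.

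A reader might infer three stronger things that the documents do not support:

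- **That the inflation error produced the dz≥0.70 statement.** It did not. The printed table already lists 21, 23 and 25 recruits for dz=0.7, so the gap at N=20 is visible before any correction.
- **That the statement fails as soon as a second participant drops out, because 19 pairs are required.** With 18 pairs the power at dz=0.70 is 79.9%, which the word approximately covers.
- **That the definitive trial will be sized from Table 2.** Power Calculation and Statistical Methods both name the pilot's observed variance and effect sizes as the inputs. Carrying the (1+d) rule forward is a risk, not a stated plan.

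It could also be said that the mixed models use first-period data from dropouts. Table 2, however, is defined in completed pairs, so that does not rescue its recruit columns.

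**Conclusion.** The recruit columns of Table 2 are wrong as written. The rule used is n×(1+d), and 14 of 15 cells are too low by 1 to 7 recruits (13 of 15 if n/(1−d) is rounded to nearest). In the 30% column this leaves power of about 74% to 79% instead of 80%.

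The power statement for 20 recruits is a separate and weaker point. It is not false, but it is incomplete: fair from no dropout to about 10%, and optimistic at the 20% and 30% that the table itself considers. The documents set no expected dropout rate, so they do not show which of these cases applies.

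Severity is minor to moderate. The pilot's size, conduct and feasibility conclusions do not depend on Table 2. The reasons to correct it are that the stated figures are wrong and that the rule should not pass into the definitive trial, where it would give 96% of the required completers at 20% dropout and 91% at 30%.

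These conclusions assume a two-sided paired t test at 0.05, as the section describes, and that a participant who drops out contributes no completed pair, as the table defines.

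**What to change.** 1. Replace the three recruit columns of Table 2 with n/(1−d) rounded up, for 10/20/30% dropout: dz 0.4: 58/65/75; dz 0.5: 38/43/49; dz 0.6: 27/30/35; dz 0.7: 22/24/28; dz 0.8: 17/19/22. State the formula under the table. The completed-pairs column stays.
2. In Power Calculation and in Statistical Methods, attach the dropout rate to the power statement, for example: 20 recruits give 80% power for dz of about 0.66 with no dropout, 0.70 at 10% (18 pairs), 0.75 at 20% (16 pairs) and 0.81 at 30% (14 pairs).
3. Keep N=20, and use n/(1−d) when the definitive trial is sized.

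The cost is one table and two sentences. Recruitment, conduct and analysis do not change; the stated power only becomes slightly less favourable at higher dropout.

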### Statistical Methods

This study is a 2-period, 2-sequence crossover pilot trial without a washout period between treatments. Analyses will primarily focus on feasibility outcomes (recruitment, adherence, data completeness, and dropout) using descriptive statistics (means, medians, and proportions) with 95% CIs rather than formal hypothesis testing. These feasibility metrics will inform the practicality of conducting a larger definitive trial.

For the primary clinical outcome of pain intensity, exploratory analyses will first be conducted using paired *t* tests to compare mean scores between TENS and TENS with self-selected music within participants. Normality of paired differences will be assessed using graphical methods and the Shapiro-Wilk test. If assumptions are violated, the Wilcoxon signed-rank test will be applied as a nonparametric alternative. Categorical variables (eg, adverse events and compliance categories) will be analyzed initially using chi-square tests, or Fisher exact test if expected cell counts are small. All tests will be 2-sided with a significance level of *α*=.05.

Following these preliminary analyses, formal modeling tailored to the crossover design will be undertaken. Linear mixed-effects models will be specified with fixed effects for treatment (TENS vs TENS with self-selected music), period, and sequence, and a random intercept for participant to account for within-participant correlations. Because no washout period is present, carryover effects will be explicitly assessed by including a prior-treatment term and by examining period×sequence interactions. If evidence of carryover is observed, analyses will be restricted to first-period data as a sensitivity check, treating it as a parallel-group comparison.

Secondary outcomes (mood, function, satisfaction, medication use, and adverse events) will be analyzed using appropriate mixed-effects regression models: linear for continuous outcomes, cumulative logit for ordinal outcomes, negative binomial for counts, and logistic for binary outcomes. These analyses are exploratory in nature. Given the pilot design and small sample size, no formal correction for multiple testing will be applied; instead, effect sizes and CIs will be reported to guide future sample size calculations.

Intention-to-treat principles will be followed, analyzing participants according to their randomized sequence regardless of adherence or protocol deviations. Mixed-effects models allow inclusion of all available data, including partial data from participants who drop out after the first period, thereby minimizing bias. Per-protocol analyses will be conducted as sensitivity checks. Missing data will be handled descriptively, with analyses restricted to available cases. No multiple imputation will be attempted due to the small sample size.

As a feasibility study with 20 participants, the trial is powered only to detect large effects (approximately dz≥0.70). The observed variance and effect sizes will be used to refine sample size calculations for the definitive trial.

All analyses will be conducted using Stata and SPSS Statistics (IBM Corp).

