## Methods

### Overview

TENS with music study will be a prospective, randomized controlled pilot study to compare TENS alone to TENS combined with participant self-selected music. The participants will be randomized to receive 2 weeks of TENS therapy and 2 weeks of TENS with self-selected music using a streaming service, CD player, Long Play, or radio. The order in which this is delivered will be determined by randomization. Therefore, 1 group will receive standard TENS for 2 weeks, followed by TENS with self-selected music for 2 weeks. This order will be reversed in the other group with no washout period. The participants will be compared against themselves for the outcomes, thus reducing the number of participants to power the study. We are hoping to recruit 20 participants for this pilot trial (Figure 1). We will use TENS and TENS with music as part of a holistic pain management plan involving pain neuroscience education, behavior activation, and coping skills training that is individually tailored and not as a stand-alone intervention for pragmatic reasons.

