### Randomization

Participants will be randomized in a 1:1 ratio to 1 of 2 treatment sequences:

Sequence AB: 2 weeks of standard TENS followed by 2 weeks of TENS combined with self-selected musicSequence BA: 2 weeks of TENS combined with self-selected music followed by 2 weeks of standard TENS

Randomization will be performed using a computer-generated allocation list created in Stata (StataCorp LLC) before study commencement. A permuted block design with variable block sizes will be used to ensure balance between sequences throughout recruitment. The randomization seed and code will be archived to allow reproducibility. Allocation concealment will be maintained by storing the randomization list in the Research Electronic Data Capture (REDCap; Vanderbilt University) randomization module, which will reveal the assigned sequence only after a participant has provided informed consent and completed baseline assessments.

The randomization result will be communicated to participants by telephone within 24 hours of their initial assessment. Investigators responsible for outcome collection and statistical analysis will remain blinded to treatment sequence. Participants cannot be blinded due to the pragmatic nature of the intervention.

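### Chi-square and Fisher tests ignore the crossover pairing and are the only tests named for compliance categories; for pain, the period-adjusted model should be named as the lead result

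*Protocol article*

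**What the plan says.** The Statistical Methods section of the protocol article states the design plainly: "This study is a 2-period, 2-sequence crossover pilot trial without a washout period between treatments". The Overview adds: "The participants will be compared against themselves for the outcomes".

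The analysis then has two stages.

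- **First stage, two-sided 0.05.** For pain, "exploratory analyses will first be conducted using paired" t tests, with the Wilcoxon signed-rank test as fallback. Categorical variables, with adverse events and compliance categories as the examples, "will be analyzed initially using chi-square tests, or Fisher exact test if expected cell counts are small". No paired categorical test is named, and nothing at this stage has a period term.
- **Second stage.** Pain gets a linear mixed model with treatment, period, sequence and a random participant intercept. Mood, function, satisfaction, medication use and adverse events get mixed-effects models suited to their type, logistic for binary outcomes. Compliance categories are not in that list.

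The Power Calculation section gives estimation of variance as one purpose of the pilot. The end of Statistical Methods says that the observed variance and effect sizes will feed the sample size of the definitive trial. Neither place says which analysis supplies them.

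**The concern.** The first stage respects the pairing for pain but not for categorical outcomes. If 20 participants each give one response under each treatment, a table of treatment by response has 40 entries from 20 people. Chi-square and Fisher tests take those entries as independent. When a participant's two responses are positively correlated, the tests overstate the variance of the treatment difference, so a real difference in adverse events or compliance is harder to see. Compliance bears on the first hypothesis, that the combination is as feasible as TENS alone.

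For pain, the paired t test handles the pairing but not the period. A period effect is plausible here: previous TENS users are excluded, so participants are learning the device, and treatment sits within a "holistic pain management plan involving pain neuroscience education, behavior activation, and coping skills training". Two pain results will exist, one with and one without a period term, and neither is named as the lead or as the source of the variance to carry forward.

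**Working it through.** **Inputs from the protocol.** Target of 20 participants ("As a pilot study (target recruitment N=20), the trial is adequately powered only for larger effects"); "Participants will be randomized in a 1:1 ratio to 1 of 2 treatment sequences", so 10:10 is expected; planning "with a 2-sided *α*=.05 and 80% power"; dz of about 0.70 as the detectable effect; a 2-point difference on the pain scale called significant in the Aims.

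**Assumptions.** The protocol gives no event rates, within-participant correlation or period effect, so ranges are shown. The SD of the paired difference is taken as 2/0.70 = 2.86.

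**1. The plan's own figures.** Paired t test power from the noncentral t distribution gives 52, 34, 24, 19 and 15 completed pairs for dz 0.4 to 0.8, exactly as in Table 2. Twenty completed pairs at dz 0.70 give 84% power.

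**2. One categorical example.** Take 12/20 v 6/20 with six discordant participants, all in the same direction.

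- Chi-square, uncorrected: 40 × (12×14 − 8×6)² / (20×20×18×22) = 3.64, p=0.057.
- Fisher: p=0.11.
- Exact McNemar: 2 × (1/2)⁶ = 0.031.
- Mid-p McNemar: 0.031 less the probability of the observed split, (1/2)⁶ = 0.016, giving 0.016.

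This is the pattern most favourable to a paired test, so it shows that the choice can matter, not how often it will.

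**3. Rejection rates for 20 pairs by exact enumeration, nominal 5%, no true difference, both rates 0.5.**

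| Correlation of the two responses | Chi-square | Fisher | Exact McNemar | Mid-p McNemar |
|---|---|---|---|---|
| 0 | 4.3% | 2.0% | 2.3% | 4.2% |
| 0.3 | 1.7% | 0.6% | 1.7% | 3.6% |
| 0.5 | 0.5% | 0.2% | 0.9% | 2.6% |
| 0.7 | 0.06% | 0.01% | 0.2% | 0.9% |

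With both rates 0.2 and correlation 0.5, the four figures are 0.8%, 0.2%, 0.2% and 1.0%. Exact McNemar is itself well below 5%, so part of the shortfall is small-sample discreteness and not the lost pairing.

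**4. Power for 0.5 v 0.8.**

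| Correlation | Chi-square | Fisher | Exact McNemar | Mid-p McNemar |
|---|---|---|---|---|
| 0 | 53% | 41% | 37% | 47% |
| 0.3 | 53% | 38% | 48% | 61% |
| 0.5 | 52% | 36% | 58% | 76% |

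The loss from ignoring the pairing grows with the correlation. At zero correlation there is none.

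**5. Pain, 10:10.** A period effect π adds +π to the treatment difference in one sequence and −π in the other. Ignoring it multiplies the variance of the paired differences by about 1 + (π/2.86)². (At n=20 the sample variance carries a further factor 20/19 on the second term, a small change.)

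| Period effect | Variance factor | Power, paired t | Power, period-adjusted |
|---|---|---|---|
| 0 | 1.00 | 84% | 84% |
| 1 point | 1.12 | 81% | 84% |
| 2 points | 1.49 | 71% | 84% |

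At dz 0.70 with no period effect, the period term changes power from 0.844 to 0.841.

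**6. Bias.** The paired mean shifts by π × (n_AB − n_BA)/n. At 10:10 this is zero. With an assumed 10 v 6 completers and π = 1 it is 1 × 4/16 = 0.25 points. The period-adjusted estimate is unbiased in both cases.

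**The case against.** The plan calls these tests initial, preliminary and exploratory, and the same section then specifies modelling built for a crossover. Adverse events get a mixed-effects model, and the pain model contains the period term. Feasibility outcomes are descriptive, and progression rests on the 80% thresholds, so no decision turns on a chi-square p value. With positive correlation the error runs towards missed differences and not false positives. All of this stands, and it limits the weight of the point.

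The text also does not say that the chi-square contrast is between treatments. Compliance with other interventions, as listed under Outcomes, could be one value per participant. A comparison of sequences on one value each would be valid, but it would not estimate the treatment effect. The point therefore applies where treatments are compared.

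A reader might infer three stronger things that the document does not support:

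- **That the reported adverse-event analysis is invalid.** Only its first stage is unsuitable; the later model accounts for the pairing.
- **That the planning SD will contain the period effect.** No section takes that SD from the paired t test. The source is simply not named.
- **That uneven dropout will bias the treatment estimate.** This affects only the unadjusted t test, and only if sequences complete unequally. The mixed model has a period term and keeps first-period data from those who drop out.

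**Conclusion.** The point holds in limited form. Chi-square and Fisher tests are the wrong stated method for comparing treatments within participants. For compliance categories no other test is named, so the defect is not made good later; for adverse events it is. The consequence is lost sensitivity, and its size depends on an unknown correlation: at 0.5 v 0.8, chi-square has 52% power against 76% for mid-p McNemar when the correlation is 0.5, but no disadvantage when it is zero.

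For pain the right model is already planned, and what is missing is its status. The unadjusted t test costs power if there is a period effect (81% at 1 point and 71% at 2 points, against 84%). Those period effects and the SD of 2.86 are assumptions, and 2 points is as large as the whole difference that the Aims call significant.

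**What to change.** 1. For categorical comparisons between treatments, replace chi-square and Fisher with a paired test. Mid-p McNemar is preferable to the exact version, which is also conservative at n=20. Mainland-Gart also allows for period, but it needs enough discordant pairs: six, split 3:3 by sequence and all favouring one treatment, give a Fisher p of 2/20 = 0.10.
2. Add compliance categories to the outcomes covered by the mixed-effects models, and say whether compliance is recorded per period or once per participant.
3. For pain, name the treatment, period and sequence model as the lead result and as the source of the variance for the definitive trial. Label the paired t test (and signed-rank test) as descriptive.

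The cost is a few sentences of analysis wording and one degree of freedom for the period term, with no change to recruitment or data collection unless compliance is not now recorded per period.

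### The planned carryover checks are aliased with terms already in the crossover model, so they cannot tell whether carryover occurred and should not trigger a first-period analysis

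*Protocol article*

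**What the plan says.** Statistical Methods describes the design: "This study is a 2-period, 2-sequence crossover pilot trial without a washout period between treatments". Randomization assigns participants 1:1 to TENS then TENS with music (AB), or to "2 weeks of TENS combined with self-selected music followed by 2 weeks of standard TENS" (BA).

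The mixed model has "fixed effects for treatment (TENS vs TENS with self-selected music), period, and sequence, and a random intercept for participant". For carryover, Statistical Methods adds that "carryover effects will be explicitly assessed by including a prior-treatment term and by examining period×sequence interactions". The consequence follows: "If evidence of carryover is observed, analyses will be restricted to first-period data as a sensitivity check, treating it as a parallel-group comparison". The article does not say that treatment or sequence is taken out when the carryover terms go in, and it describes no carryover term limited to part of a period.

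**The concern.** An AB/BA trial has only four sequence-by-period means. A model with an intercept, treatment, period and sequence already fits all four exactly. A further term defined at the level of the whole period has nothing left to estimate, yet the plan adds two such terms and lets the result decide whether a first-period analysis is done.

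This matters because these checks are the analytic safeguard that the article offers for having no washout. The Discussion (Anticipated Findings) itself calls the duration of music analgesia in chronic pain unclear. Power Calculation and Statistical Methods also name the observed effect size and variance as inputs to the definitive trial. A check that carries no information on carryover could report a problem that does not exist, or appear to clear one that does. Choosing an analysis by a pretest also distorts the error rate of what is then reported.

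**Working it through.** **Inputs.** Two sequences and two periods (Randomization; Statistical Methods); N=20, so 10 per sequence; two-sided alpha 0.05; dz=0.70, the effect for which Power Calculation calls the trial adequately powered. The article gives no variance or within-person correlation. I assume correlations (rho) of 0.3, 0.5 and 0.7, equal variances and complete data.

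**The plan's own figures.** Exact noncentral-t power for a paired t test reproduces the completed pairs in Table 2: 52, 34, 24, 19 and 15 for dz 0.4 to 0.8. At 20 pairs and dz=0.70, power is 84.4%.

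**Aliasing.** Code T=1 for music, P=1 for period 2 and S=1 for BA.

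| Cell | T | P | S | P×S | Prior music |
|---|---|---|---|---|---|
| AB, period 1 | 0 | 0 | 0 | 0 | 0 |
| AB, period 2 | 1 | 1 | 0 | 0 | 0 |
| BA, period 1 | 1 | 0 | 1 | 0 | 0 |
| BA, period 2 | 0 | 1 | 1 | 1 | 1 |

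- In every row T = P + S − 2(P×S), and prior music = P×S = (P + S − T)/2.
- {1, T, P, S} has 4 columns and rank 4. Adding prior music, or P×S, gives 5 columns and rank 4.
- With weekly rows, week effects and period-level carryover terms, either addition gives 7 columns and rank 6.

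**What each way of running it does.**

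1. *Treatment, period and sequence kept.* The added term is omitted as collinear and no carryover test results.
2. *Period×sequence examined without treatment.* Its coefficient is (BA2 − BA1) − (AB2 − AB1) = (P − T) − (P + T) = −2T, where P and T now stand for the period and treatment effects. It is the treatment contrast, rescaled. In 20,000 simulated trials per scenario with no carryover, it was significant in about 5% of trials at dz 0, 56% at dz 0.5, 84% at dz 0.7 and 99% at dz 1.0.
3. *Prior treatment replaces sequence.* The cell means are AB1 = a, AB2 = a + T + P, BA1 = a + T and BA2 = a + P + C, where C is the carryover effect. Hence T = BA1 − AB1, the first-period difference between groups, and C = (BA1 + BA2) − (AB1 + AB2), a between-participant contrast of sequence totals.

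**The analysis that would be triggered.** For 10 v 10 in period 1, d = 0.70 × √(2(1 − rho)), the noncentrality is d × √(10/2), and there are 18 degrees of freedom.

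| rho | d | Noncentrality | Power |
|---|---|---|---|
| 0.3 | 0.83 | 1.85 | 42% |
| 0.5 | 0.70 | 1.57 | 32% |
| 0.7 | 0.54 | 1.21 | 21% |

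The paired analysis has 84%.

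**The case against.** A reader might infer that, under the plan as written, any real benefit of music will be labelled carryover. The article does not support that. It keeps treatment as a fixed effect, and then the added term drops out and nothing is triggered. The 84% holds only where period×sequence is examined without treatment, which the article neither states nor rules out.

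A reader might also infer that carryover cannot be estimated from this trial at all. That too goes beyond the document. Three routes exist:

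- Dropping sequence makes a prior-treatment term estimable (rank 4 of 4), if there is no true sequence effect. A treatment benefit does not set it off: about 5% of trials are significant at every dz tried. It is weak, with about 9–10% power for a 1-point carryover at an assumed SD of 2.
- A term confined to week 3 of the weekly pain scores has full rank (7 of 7).
- Using the baseline week as an extra row gives rank 6 of 6.

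Statistical Methods specifies none of these, so they do not rescue its wording, but they limit what may be said against the design.

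Other mitigation stands. The primary outcome is feasibility, analysed descriptively; the pain analyses are exploratory; paired tests come first, whatever the carryover check shows; and the first-period analysis is labelled a sensitivity check. Anticipated Findings also argues that carryover is small, since TENS analgesia usually fades by 24 hours and music effects are short-lived.

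**Conclusion.** The carryover checks are invalid as written. This is exact algebra and rests on no assumed figure. Depending on how the wording is implemented, the check is empty, repeats the treatment test, or turns the model's treatment coefficient into a first-period comparison.

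The size is conditional. The figure of about 84% needs dz=0.70, 20 completers, no carryover and treatment left out of the model. The first-period powers of 42%, 32% and 21% rest on the assumed correlations.

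The wording should be corrected, but the pilot's main purpose is not threatened. No feasibility criterion changes, and the paired comparison remains available. What is exposed is any statement about carryover, and the effect size taken forward to the larger trial.

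**What to change.** - Delete the period×sequence test, the period-level prior-treatment term and the rule that makes the first-period analysis depend on evidence of carryover.
- Name treatment + period + sequence with a participant random intercept as the crossover model.
- State that, with period-level terms in the two treatment periods, carryover cannot be separated from a sequence effect or from treatment-by-period interaction. Rest the case for small carryover on the short-duration argument in Anticipated Findings.
- Always report, without a pretest, the first-period difference as a description.
- For pain-score and diary outcomes only, also always report a sensitivity estimate from weeks 2 and 4, which leaves 7 days after the switch. By Table 1, the functional and mood scales are already measured only at those weeks after baseline, so it adds nothing there.
- If a carryover term is wanted, use an estimable one, such as a term confined to week 3 of the weekly pain scores. Report its estimate and CI, and do not use it to choose the analysis.

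The cost is a few sentences and slightly more analysis, with no new data or participants. The price is that no formal carryover test remains. With 4 of 20 participants enrolled at submission and analysis due by December 2026 (Results), the change can be made before the data are analysed.
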